The primary endpoint of this study is safety assessed from the start of radiotherapy until the first follow up after surgery (4–6 weeks after surgery). Based on experience from clinical practice, the number of patients lost to follow-up is expected to be very small. Patients who dropped out of the study between radiation treatment and first follow-up visit will be replaced by a new patient. For patients without a final examination after 1 year, the last valid examination will be used for the assessment of secondary endpoints. All secondary endpoints will be analyzed in an explorative manner using appropriate statistical methods: Mann–Whitney *U* Test (acute toxicity of CTCAE grade 1–3; late toxicity of CTCAE grade 1–5, immunological parameters, time interval between treatment initiation and start of systemic chemotherapy), Fisher’s exact test or Chi-square test (local control rates), log-rank test and Kaplan–Meier curves (OS and PFS at 12-month follow-up), Student *t* test (neurocognitive function), and scaled *t* test (health-related QoL) for independent patients.

The following parameters will be collected and taken into account in analyses applying regression models: age, Karnofsky performance score, extent of neurosurgical resection, recursive partitioning analysis (RPA)-classification.

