### Assessment of endpoints

The primary endpoint, MTD, will be assessed through extensive anamnesis and clinical neurological examination on the first postoperative day, the day of discharge from hospital, and the first follow-up visit at 4–6 weeks after surgery, with wound healing evaluated by an experienced neurosurgeon. This study will use the CTCAE version 5.0 for toxicity and adverse event reporting. Postoperative MRI (1–2 days after surgery) and the first follow-up MRI (4–6 weeks after surgery) will be evaluated by an experienced neuroradiologist, and the efficacy will be assessed according to the RECIST criteria [34].

For secondary endpoints, anamnesis and clinical neurological examination will be conducted as mentioned above. Disease progression is defined as radiological or neurological/clinical progression (whichever occurs first); PFS is considered the time interval between the date of treatment initiation and the date of disease progression or death, whichever occurs first. If neither event is observed, the patient will be censored at the date of the last follow-up examination. Neurocognitive function, QoL, and late toxicities will be evaluated at each follow-up visit every 3 months or at neurological deterioration (Table 2). Neuropathological work-up on the resected specimen will follow standard operating procedures at the Department of Pathology and will include immunologic as well as molecular parameters, such as PD-L1 expression, BRAF-gene mutation, EGFR mutation, and ALK translocation, where appropriate. Follow-up assessments (including MRI or CT) will be performed as described until disease progression (even after the termination of the study) in accordance with GCP and the treatment guidelines for patients with intracerebral metastases.

**Table 2 Tab2:** Time schedule of this study

Timepoint	Enrollment	Treatment				Follow-up (months)				Close-out (months)
	Day 0	Preoperative RT Day 1	Resection Days 2–7	Postoperative Days 1–2	Postoperative Days 3–5	1,5	3	6	9	12
Enrollment										
Eligibility screening	X									
Informed consent	X									
Study visit	X	X			X	X	X	X	X	X
Planning CT	Within 1–7 days after enrollment									
Planning MRI	Within 1–7 days after enrollment									
Interventions										
Neoadjuvant SRS		X								
Resection			X							
Assessments										
MRI	X			X		X	X	X	X	X
Clinical-neurological examination	X	X	X	X	X	X	X	X	X	X
Minimental state examination	X					X	X	X	X	X
Health-related QoL	X				X	X	X	X	X	X

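### Carrying the last examination forward to one year counts living patients who are no longer imaged as locally controlled, so 12-month local control is overstated whenever there are such patients

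*Protocol article*

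**What the plan says.** The missing-data rule stands in Statistical analyses: "For patients without a final examination after 1 year, the last valid examination will be used for the assessment of secondary endpoints". No secondary endpoint is excepted.

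The same section analyses local control with Fisher's "exact test or Chi-square test (local control rates"), which compares proportions without censoring. For the two patient-function endpoints it names "Student *t* test (neurocognitive function), and scaled *t* test (health-related QoL").

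Assessment of endpoints states how long assessments run: "Follow-up assessments (including MRI or CT) will be performed as described until disease progression (even after the termination of the study"). Progression is not limited to the treated site: "Disease progression is defined as radiological or neurological/clinical progression (whichever occurs first"). PFS has its own rule: "If neither event is observed, the patient will be censored at the date of the last follow-up examination". OS and PFS are analysed by Kaplan–Meier and log-rank.

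Table 2 lists MRI, MMSE and quality of life at 1.5, 3, 6, 9 and 12 months and shows no stop at progression. The text adds: "Neurocognitive function, QoL, and late toxicities will be evaluated at each follow-up visit every 3 months or at neurological deterioration".

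The section Data collection, management, and analysis says that the data of a participant who discontinues will not be used for analysis.

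**The concern.** Local control is a time-to-event outcome seen only on scans. If a patient's last scan is at month 3 and shows control, the rule reports control at month 12. A later local failure in that patient cannot enter the numerator, yet the patient stays in the denominator. The error can go only one way for local control: an unseen failure is always scored as control.

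The plan may itself create such patients. Distant or clinical progression meets the definition of progression, and the text commits to no imaging after it. OS and PFS are protected by censoring. Local control has the same incomplete follow-up and is not protected.

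At stake are the 12-month local control rate and, with less certainty, the year-one figures for MMSE, quality of life and late toxicity. The article's Background calls long-lasting local control increasingly important, and its Discussion names good local control as an aim.

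**Working it through.** **The plan's own figures.** The article gives no power, effect size or progression rate for these endpoints. Its sample sizes reproduce: 4 × [(3 × 3) + 3] = 48 and 4 × 6 × 3 = 72. The point does not rest on them.

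**Inputs.**
- Local control of 97.8% at 6 months and 85.6% at 12 months, from the neoadjuvant series quoted in the Discussion, taken as the truth for illustration.
- Share of patients q whose imaging stops by month 12: 30%, 50% or 70%. Assumed.
- Stopping at a constant rate, independent of local failure. Assumed.
- Share of stopping that is death: none, half or all. Assumed.

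**Local-failure hazard per month.**
- Months 0–6: h1 = −ln(0.978)/6 = 0.00371
- Months 6–12: h2 = −ln(0.856/0.978)/6 = 0.02221

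**Stopping hazard.** s = −ln(1 − q)/12 = 0.0297, 0.0578 and 0.1003 per month for q = 0.3, 0.5 and 0.7.

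**Failures by month 12 that occur before a competing process of rate r:**

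F(r) = h1/(h1+r) × [1 − e^(−6(h1+r))] + e^(−6(h1+r)) × h2/(h2+r) × [1 − e^(−6(h2+r))]

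With r = 0 this returns 0.022 + 0.122 = 0.144, that is, 85.6% control. Carry-forward counts F(s). The target is the cumulative incidence with death as competing event: F(0) if no stopping is death, F(s/2) if half is, F(s) if all is.

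| q | Counted F(s) | Reported control | Target, none death | Overstatement | Target, half death | Overstatement |
|---|---|---|---|---|---|---|
| 30% | 0.114 | 88.6% | 0.144 | 3.0 points | 0.128 | 1.4 points |
| 50% | 0.092 | 90.8% | 0.144 | 5.2 points | 0.115 | 2.3 points |
| 70% | 0.067 | 93.3% | 0.144 | 7.7 points | 0.097 | 3.0 points |

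With no deaths, 21%, 36% and 53% of local failures go unseen; with half deaths, 11%, 20% and 31%. If all stopping is death, target and count coincide and the overstatement is zero.

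In patients, 3.0 points of 48 is 0.030 × 48 = 1.4, and 7.7 points of 72 is 0.077 × 72 = 5.5.

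**Check on the visit schedule.** A simulation used scans at 1.5, 3, 6, 9 and 12 months and assumed non-local progression in 20%, 40% or 60% of patients by month 12, all alive.
- If the scan at the progression visit is still done, carry-forward gives 87.2%, 89.1% and 91.1%, which is 1.6, 3.5 and 5.5 points too high.
- If clinical progression ends imaging before the next scan, it gives 87.9%, 90.3% and 92.8%, which is 2.3, 4.7 and 7.2 points too high.
- Censoring at the last scan returns 85.6% in all six cases.

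**MMSE, quality of life, late toxicity.** No arithmetic is possible. In the second simulated case about 11%, 23% and 37% of patients would have a value from month 3 or earlier standing for month 12. Whether that value is too good or too bad depends on whether the last examination was a routine one or one prompted by deterioration.

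**The case against.** *Imaging does not stop at progression.* The follow-up sentence can be read as extending follow-up beyond month 12, and Table 2 shows no stop. This stands in part. A reader might infer that the plan forbids scans after progression, and the article does not say that. It leaves them uncommitted in one place and scheduled in another. Even if every visit continued, the rule would still apply to living patients who miss the month-12 scan.

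*Loss to follow-up is negligible.* The article says that "the number of patients lost to follow-up is expected to be very small". It gives no figure, and this does not address assessments that end because of progression.

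*Deaths make the rule harmless.* This stands for those who die without local failure: counting them as free of failure agrees with a competing-risk analysis. The bias comes only from patients who are alive and unimaged, so the no-death figures are the top of the range under these assumptions.

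*MMSE, quality of life and late toxicity will look too good.* A reader might infer this, but the article does not support it. These are also assessed at neurological deterioration, so the value carried forward may be the worst one.

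*Comparison with the quoted series becomes invalid.* This also goes too far. The article does not say how those rates were estimated, and it plans no formal comparison with them.

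*The endpoints are exploratory.* True, and this limits the weight of the point. But the carry-forward rule is fixed in the protocol text, so an analysis plan that follows it would inherit the bias.

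**Conclusion.** The point holds for local control. As written, the rule scores a living patient without later imaging as controlled at 12 months, and the error can only raise the reported rate. Under the assumptions shown, the overstatement runs from zero (all stopping is death) through 1.4 to 3.0 points (half) to 3.0 to 7.7 points (none). The stopping rates, the share of deaths and the independence of stopping from local failure are assumptions that the article cannot settle.

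For MMSE, quality of life and late toxicity, early values may stand for month 12, with a bias of unknown direction. The endpoints are secondary and exploratory. The MTD rests on the window to the first follow-up visit, and OS and PFS use Kaplan–Meier methods; none of these is affected.

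Two inconsistencies come with the point: the follow-up sentence against Table 2, and the exclusion of discontinued participants' data against the carry-forward of their last examination.

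**What to change.** - Delete the carry-forward sentence in Statistical analyses.
- Report local failure as cumulative incidence from SRS, with death without local failure as competing event and censoring at the last MRI, at 6 and 12 months. Treat late toxicity likewise, censored at the last visit.
- Analyse MMSE and quality of life on all observed visits with a repeated-measures model, and give the numbers alive and assessed at each visit.
- Reconcile Assessment of endpoints with Table 2 on whether scheduled assessments run to month 12 after non-local progression. Settle this early, because scans not obtained cannot be recovered.
- Reconcile the rule on discontinued participants in Data collection, management, and analysis with Statistical analyses, so that it is clear whose data are used and up to when.

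The analysis changes cost a little extra work and probably a somewhat lower reported local control rate. Settling the assessment schedule is a protocol change, not only analysis wording. If visits after progression are confirmed, they are ones that Table 2 already lists.

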### Assessment of endpoints

The primary endpoint, MTD, will be assessed through extensive anamnesis and clinical neurological examination on the first postoperative day, the day of discharge from hospital, and the first follow-up visit at 4–6 weeks after surgery, with wound healing evaluated by an experienced neurosurgeon. This study will use the CTCAE version 5.0 for toxicity and adverse event reporting. Postoperative MRI (1–2 days after surgery) and the first follow-up MRI (4–6 weeks after surgery) will be evaluated by an experienced neuroradiologist, and the efficacy will be assessed according to the RECIST criteria [34].

For secondary endpoints, anamnesis and clinical neurological examination will be conducted as mentioned above. Disease progression is defined as radiological or neurological/clinical progression (whichever occurs first); PFS is considered the time interval between the date of treatment initiation and the date of disease progression or death, whichever occurs first. If neither event is observed, the patient will be censored at the date of the last follow-up examination. Neurocognitive function, QoL, and late toxicities will be evaluated at each follow-up visit every 3 months or at neurological deterioration (Table 2). Neuropathological work-up on the resected specimen will follow standard operating procedures at the Department of Pathology and will include immunologic as well as molecular parameters, such as PD-L1 expression, BRAF-gene mutation, EGFR mutation, and ALK translocation, where appropriate. Follow-up assessments (including MRI or CT) will be performed as described until disease progression (even after the termination of the study) in accordance with GCP and the treatment guidelines for patients with intracerebral metastases.

**Table 2 Tab2:** Time schedule of this study

Timepoint	Enrollment	Treatment				Follow-up (months)				Close-out (months)
	Day 0	Preoperative RT Day 1	Resection Days 2–7	Postoperative Days 1–2	Postoperative Days 3–5	1,5	3	6	9	12
Enrollment										
Eligibility screening	X									
Informed consent	X									
Study visit	X	X			X	X	X	X	X	X
Planning CT	Within 1–7 days after enrollment									
Planning MRI	Within 1–7 days after enrollment									
Interventions										
Neoadjuvant SRS		X								
Resection			X							
Assessments										
MRI	X			X		X	X	X	X	X
Clinical-neurological examination	X	X	X	X	X	X	X	X	X	X
Minimental state examination	X					X	X	X	X	X
Health-related QoL	X				X	X	X	X	X	X
Toxicities	X				X	X	X	X	X	X
Adverse events		Continuous assessment				X	X	X	X	X

This table of study schedule is based on the the SPIRIT© checklist, minor changes were made for adaption to the NepoMUC protocol

*CT* computer tomography, *MRI* magnetic resonance tomography, *SRS* stereotactic radiosurgery

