### Study design

The trial is designed as a single-center, dose escalation study. Patients fulfilling the inclusion and exclusion criteria will be allocated to neoadjuvant SRS and assigned to four different cohorts depending on tumor size. Within each cohort, there are 3 different dose levels. The treatment contains neoadjuvant SRS according to the protocol, tumor resection according to imaging findings, and postoperative neuropathological evaluation.

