### Patient selection

Patients with the diagnosis of intracerebral metastasis on contrast-enhanced MRI will be evaluated and screened for the protocol. All patients fulfilling the inclusion and exclusion criteria will be informed about the study. Registration for the study must be performed prior to the initiation of RT. The study treatment (neoadjuvant SRS and/or neurosurgical intervention) should be initiated no later than 3 weeks after diagnosis of intracerebral metastases.

Patients meeting all of the following inclusion criteria will be considered for admission to the trial:Patients with 1–4 intracerebral metastases observed on contrast-enhanced MRI from histologically confirmed solid tumors.One intracerebral metastasis is ≥ 3 cm in diameter orPersisting neurologic symptoms or symptomatic epilepsy from intracerebral metastases despite treatment with steroids.Tumor location close to eloquent brain areas therefore neurological symptoms can be expected without long-term steroidal medication.Patient decides to undergo surgical intervention, if resection and radiotherapy are equal treatment options or if the patient declines radiotherapy.
Age ≥ 18 years of age.Karnofsky performance score ≥ 70, Eastern Cooperative Oncology Group (ECOG) performance score ≤ 1.Women with childbearing potential should have adequate contraception.Ability of subject to understand character and individual consequences of the clinical trial.Written informed consent (must be available before enrolment in the trial).

Patients presenting with any of the following exclusion criteria will not be included in the trial:Patients with unknown primary tumor.The diameter of any single lesion exceeding 4 cm.Tumors causing severe neurological deficits or with mass effect requiring immediate surgical intervention.Previous radiotherapy to the brain.Known histological type of small cell cancer, germ cell cancer, or lymphoma.Patient refuses to take part in the study.Patients who have not yet recovered from acute toxicities of prior therapies.Clinically active renal, liver, or cardiac disease.Known carcinoma within 5 years (excluding carcinoma in situ of the cervix, basal cell carcinoma, squamous cell carcinoma of the skin) requiring immediate treatment that interferes with the study therapy.

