#### Dose prescription

Neoadjuvant SRS is applied in a single fraction with single doses depending on the volume and location of the intracerebral metastases requiring neurosurgical resection. The starting dose for the dose escalation scheme will be the dose used by Asher et al. [21] that was already proven to be safe and tolerable in a neoadjuvant setting. The dose will be increased by 2 Gy increments up to the dose recommended by the DEGRO working group on SRS for intracerebral metastases (Table 1) [25]. Doses are prescribed to the 80% isodose line using a linear accelerator.

**Table 1 Tab1:** Cohorts and neoadjuvant SRS dose levels in the present study

Cohort	SRS dose level (Gy)		
	I	II	III
Lesion of ≤ 1.0 cm	18	20	22
Lesion of 1.1–2.5 cm	16	18	20
Lesion of 2.6–3.0 cm	14	16	18
Lesion of 3.1–4.0 cm	12	14	16

The patients will be assigned to 4 different cohorts depending on the largest diameter of the intracerebral metastases to be radiosurgically treated before surgical removal. Each cohort has 3 dose levels. Size and dose were chosen according to the recommondations of the German Society of Radiation Oncology (DEGRO) working group on SRS for intracerebral metastases. The first 3 patients in the first cohort will be treated at a starting dose. If no dose-limiting toxicity (DLT) occurs in that dose level, the following 3 patients will be treated at the next higher dose level; if any of the first 3 patients experiences a DLT, the following 3 patients will be treated at the same dose level. At the highest dose level, at least 6 patients will be treated. Dose will be prescribed to the 80% isodose for linear accelerator (LINAC)-based radiotherapy

*SRS* stereotactic radiosurgery

If further metastases are present (up to 4 in total, no lesion exceeding 4 cm in diameter) that do not require resection, those lesions will be treated with SRS according to the guidelines of the DEGRO working group on SRS for intracerebral metastases [25]. Quantitative analysis of normal tissue effects in the clinic (QUANTEC) reports are applied for dose constraints of normal tissues [26, 27].

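### RECIST is the only efficacy criterion named, but it is read on MRIs taken after the study lesion is resected, so a size-based response says little about the neoadjuvant SRS dose

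*Protocol article*

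**What the plan says.** All locations are in the protocol article.

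- **Criterion and scans (Assessment of endpoints).** "Postoperative MRI (1–2 days after surgery) and the first follow-up MRI (4–6 weeks after surgery) will be evaluated by an experienced neuroradiologist", and the same sentence continues that "the efficacy will be assessed according to the RECIST criteria". No other efficacy criterion is named.
- **Timing (Table 2).** "Preoperative RT Day 1 Resection Days 2–7". Resection therefore follows SRS by 1 to 6 days (2 − 1 = 1; 7 − 1 = 6).
- **Study treatment (Study design).** "The treatment contains neoadjuvant SRS according to the protocol, tumor resection according to imaging findings, and postoperative neuropathological evaluation". Resection is part of the treatment for every patient.
- **Entry (Patient selection).** "Patients with 1–4 intracerebral metastases observed on contrast-enhanced MRI from histologically confirmed solid tumors". Patients with a single metastasis are eligible.
- **Additional lesions (Dose prescription).** Metastases that do not need resection stay in place, and "those lesions will be treated with SRS according to the guidelines of the DEGRO working group". Their doses are not part of the escalation scheme in Table 1.
- **Local control.** It is listed as a secondary endpoint without a definition (Endpoints). Statistical analyses assigns it Fisher's exact test or a "Chi-square test (local control rates)", in an exploratory analysis.
- **Progression (Assessment of endpoints).** For PFS, any progression seen on imaging or clinically counts, whichever comes first. The site is not distinguished.

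**The concern.** A response criterion needs a lesion whose change can be attributed to the treatment under test. Here that lesion is taken out within a week of SRS, and both scans tied to the criterion are obtained afterwards. What remains to be measured is surgical residue, if there is any, or lesions treated by a different dosing rule.

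This matters because the Background says that durable local control is of increasing importance, and the Discussion names local control among the aims. The failure of interest after SRS and resection is recurrence at the cavity. If efficacy is reported as a RECIST response, the table will look informative by dose level while mostly describing surgery or the non-study lesions. Cavity recurrence, if captured at all, would be mixed with progression elsewhere.

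**Working it through.** **The plan's own figures.** The article gives no figure for efficacy or local control. Its only design numbers are the sample sizes, and both reproduce: 4 × [(3 × 3) + 3] = 48 and 4 × 6 × 3 = 72. Neither depends on this point.

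**Assumption.** The RECIST source cited in the article is not at hand. I assume only that a response rating compares measured lesion size with a baseline. The article does not say which scan is the baseline, so both options are checked.

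**Option 1: pre-treatment baseline.** Let S be the diameter of the study lesion and O the summed diameters of the additional lesions. With complete resection and the other lesions unchanged, the change in the sum of diameters is −S/(S + O). The diameters are illustrative and lie within the entry limit of 4 cm per lesion.

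| S (cm) | O (cm) | Change | Source of the change |
|---|---|---|---|
| any | 0 | −100% | surgery |
| 3.0 | 1.0 | −3.0/4.0 = −75% | surgery |
| 3.0 | 2.0 | −3.0/5.0 = −60% | surgery |
| 3.0 | 4.0 | −3.0/7.0 = −43% | surgery |

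If a fraction r of the diameter remains in a patient with one lesion, the change is −(1 − r). For assumed r of 0.05 to 0.30 this is −95% to −70%. The SRS dose appears in none of these expressions, so the same result follows at levels I, II and III.

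**Option 2: postoperative baseline (MRI at 1–2 days).** With complete resection the study lesion contributes zero to the baseline. Every measurable diameter then belongs to a lesion given definitive SRS outside Table 1, and a patient with one metastasis has nothing to measure. Only where residue is left does later change in a study lesion enter the rating, and how often that happens depends on surgery.

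**Cavity regrowth.** Under either option, new growth at the cavity could be noted as progression. The article does not define it, does not say how residue is to be told from recurrence, and does not separate it from progression in additional lesions or at new sites.

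**The case against.** **Local control is not expressly tied to RECIST.** The sentence speaks of efficacy on two early scans. Local control stands elsewhere as its own endpoint with its own test, and the paragraph on secondary endpoints does not mention RECIST. This stands. A reader might infer that local control will be scored by RECIST and misclassified by dose level, but the article says neither that nor that the local control comparison is by dose level. What can be said is that no other criterion is offered.

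**The full protocol may define local control.** The article refers to Version 1.1, which is not shown, and an article may leave such a definition to it. This would dispose of a complaint about missing detail. It does not dispose of this point, which concerns a criterion that is stated and does not suit the design.

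**Recurrence can still be seen.** MRI is scheduled at 1.5, 3, 6, 9 and 12 months, and progression on imaging counts for PFS. This also stands. A reader might infer that cavity control cannot be captured at all. That is too strong: it can be recorded, but it is not isolated.

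**Resection may be incomplete.** The plan collects extent of resection as a regression covariate and requires a postoperative MRI for resection control. So the study lesion is not always fully gone, which is why the conclusion is little or no information rather than none. The covariate partly acknowledges the surgical effect but does not turn a size-based response into a measure of dose.

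**The size of the harm.** It is tempting to apply the 85.6% 12-month local control of the earlier neoadjuvant SRS series cited in the Discussion. That gives 48 × 0.144 = 6.9 or 72 × 0.144 = 10.4 failures, and one could then suppose that a few are misclassified. The documents give no misclassification rate. That series also counted 51 lesions in 47 patients, with diameters up to 5.2 cm, whereas this trial excludes lesions above 4 cm. The figure should not be used as a magnitude.

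**Conclusion.** The point holds in a limited form. The one efficacy criterion named is read after resection of the study lesion. A size-based response therefore reflects the extent of surgery or the additional lesions treated outside the tested levels, and says little or nothing about the neoadjuvant SRS dose. Failure at the resection site is neither defined nor separated from other sites.

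The reach is modest. Only exploratory secondary endpoints are touched. A reader might infer that dose finding is compromised, but it is not: the MTD rests on CTCAE toxicities up to the first follow-up, and neither escalation, the recommended phase II dose nor the sample size uses local control. No number of misclassified patients can be derived.

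The conclusion rests on two assumptions: that the criterion rates change in lesion size, and that most of the study lesion is removed at surgery. It is worth correcting because the correction is cheap and local control is a stated aim.

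**What to change.** For the resected lesion, replace RECIST with local failure at the resection site, defined as either:

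- contrast enhancement in or bordering the cavity that is new or enlarging compared with the 1–2 day postoperative MRI and is judged to be tumor recurrence; or
- histological recurrence at re-operation.

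Record suspected radiation necrosis separately as toxicity and not as local failure. CNS necrosis is already a toxicity endpoint in this trial. If it rises with dose, counting every growing enhancement as failure would bias local control against the higher levels.

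Score additional lesions and new brain lesions in their own categories. Keep RECIST, if wanted, for unresected lesions only.

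**Cost.** A small change of wording and one CRF item. Table 2 already schedules the postoperative baseline MRI and the later scans to 12 months, so no scan or reader is added. The remaining downside is some uncertainty in telling recurrence from necrosis on MRI, which the definition makes visible but does not remove.
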